## Abstract

**Background:**

Carvedilol is a non-selective, third-generation beta-blocker and is one of the cornerstones for treatment for patients with heart failure and reduced ejection fraction (HFrEF). However, due to its short half-life, immediate-release carvedilol (IR) needs to be prescribed twice a day. Recently, slow-release carvedilol (SR) has been developed. The aim of this study is to evaluate whether carvedilol-SR is non-inferior to standard carvedilol-IR in terms of its clinical efficacy in patients with HFrEF.

**Methods/design:**

Patients with stable HFrEF will be randomly assigned in a 1:1 ratio to the carvedilol-SR group (160 patients) and the carvedilol-IR group (160 patients). Patients aged ≥ 20 years, with a left ventricular ejection fraction ≤ 40%, N-terminal pro B-natriuretic peptide (NT-proBNP) ≥ 125 pg/ml or BNP ≥ 35 pg/ml, who are clinically stable and have no evidence of congestion or volume retention, will be eligible. After randomization, patients will be followed up for 6 months. The primary endpoint is the change in NT-proBNP level from baseline to the study end. The secondary endpoints include the proportion of patients with NT-proBNP increment > 10% from baseline, composite of all-cause mortality and readmission, mortality rate, readmission rate, changes in blood pressure, quality of life, and drug compliance.

**Discussions:**

The SLOW-HF trial is a prospective, randomized, open-label, phase-IV, multicenter study to evaluate the therapeutic efficacy of carvedilol-SR compared to carvedilol-IR in HFrEF patients. If carvedilol-SR proves to be non-inferior to carvedilol-IR, a once-daily prescription of carvedilol may be recommended for patients with HFrEF.

**Trial registration:**

ClinicalTrials.gov, ID: NCT03209180. Registered on 6 July 2017.

**Electronic supplementary material:**

The online version of this article (10.1186/s13063-018-2470-5) contains supplementary material, which is available to authorized users.

## Background

Heart failure (HF) is a clinical syndrome characterized by typical symptoms and signs that result from abnormal cardiac structure or function [1]. It is globally present with an increasing prevalence and is associated with high morbidity and mortality [2, 3]. The current treatment of HF targets includes the prevention of acute decompensation and improving the long-term survival of HF patients [4].

Neuro-humoral activation plays a crucial role in development and progression of HF [5]. Beta-blockers reduce the increased sympathetic tone in HF patients and have been shown to improve the survival in patients with HF and a reduced ejection fraction (HFrEF) [6–8]. Carvedilol is a non-selective beta-blocker which has been most extensively studied in HF patients with mild-to-severe left ventricular (LV) dysfunction [8, 9]. Carvedilol has also shown additional mortality risk reduction in HFrEF patients compared to metoprolol [10].

Current HF guidelines recommend the administration of carvedilol twice daily [1, 11]. This is due to rapid absorption and metabolism of carvedilol whose plasma concentration reaches a peak within 1–2 h after administration and shows an elimination half-life of 7–10 h after peak concentration [12]. Although the drug compliance of carvedilol was comparable between once- and twice-daily dosing in one report [13]; however, there has been a concern that regimen complexity is inversely associated with medication adherence and related to even worse clinical outcomes in other studies and real-world clinical practice [14–16].

In the “Assessment of clinical effect and treatment quality of immediate-release carvedilol-IR versus SLOW-release carvedilol-SR in Heart Failure patients (SLOW-HF): a prospective, randomized, open-label, multicenter study,” we aim to evaluate the clinical efficacies of immediate-release carvedilol (IR) and slow-release carvedilol (SR) forms of carvedilol in Asian HFrEF patients.

## Methods/design

### Overview

The study flow is presented in Fig. 1. This trial is a prospective, randomized, open-label, phase-IV, multicenter trial to evaluate the efficacy of carvedilol-SR. The aim of this study is to evaluate whether carvedilol-SR is non-inferior to standard carvedilol-IR in terms of its clinical efficacy in patients with HFrEF. The protocol of this trial has been registered at ClinicalTrials.gov (registration number: NCT03209180). The protocol follows the Standard Protocol Items: Recommendations for Interventional Trials (SPIRIT) Checklist (Additional file 1).

**Fig. 1 Fig1:**
[figure not shown]
Study flow chart. *BNP* B-type natriuretic peptide, *HFrEF* heart failure with reduced ejection fraction, *IR* immediate-release, *LVEF* left ventricular ejection fraction, *NT-proBNP* N-terminal B-type natriuretic peptide, *SR* slow-release

### Study population

Patients who are at aged 20 years or older and with a confirmed diagnosis of HFrEF (left ventricular ejection fraction (LVEF) ≤ 40%) within the pre-analytical 6 months will be included in this study. Transthoracic echocardiography was operated at each institute according to the recommendations of the American Society of Echocardiography using commercially available systems [17]. In addition, the patients should be clinically stable without evidence of congestion and fluid retention, and have an increased level of N-terminal B-type natriuretic peptide (NT-proBNP) or BNP. Blood sampling and tests including NT-proBNP were conducted by laboratories at each participating institute which were certified by The Korean Association of Quality Assurance for Clinical Laboratory. After enrollment, measurement of NT-proBNP will be performed with an electro-chemiluminescence immunoassay method using cobas® 8000 (Roche Diagnostics, Mannheim, Germany) in a central laboratory. Patients will be enrolled at 13 tertiary referral centers in the Republic of Korea. Patients will be excluded if they have any of followings: low blood pressure (sitting systolic blood pressure < 90 mmHg), bradycardia (resting heart rate < 50 beats/min), ischemic heart disease (unstable angina, myocardial infarction) within 1 month, severe cerebrovascular accident, respiratory diseases with bronchospasm, and peripheral vascular diseases. The detailed inclusion and exclusion criteria are listed in Table 1.

**Table 1 Tab1:** Inclusion and exclusion criteria

Inclusion criteria	
1	Men or women aged 20 years or older
2	Confirmed left ventricular ejection fraction ≤ 40% by echocardiography within the pre-analytical 6 months
3	NT-proBNP level ≥ 125 pg/ml or BNP level ≥ 35 pg/ml within the pre-analytical 3 months
4	Clinically stable patient without evidence of congestion or extracellular fluid retention
5	Patients providing written informed consent
Exclusion criteria	
1	Systolic blood pressure in a sitting position < 90 mmHg or resting heart rate < 50 beats/min at screening
2	Patient has a contraindication to beta-blockers
3	Patient who are expected to take another beta-blocker after randomization
4	Cardiovascular diseases; Ischemic heart disease (unstable angina, myocardial infarction) within 1 month Hypertrophic cardiomyopathy Cor pulmonale Hemodynamically significant stenosis of the aorta, aortic valve, or mitral valve Acute myocardial infarction with complications
5	Severe cerebrovascular accident (for example, ischemic stroke or cerebral hemorrhage) within the pre-analytical within 6 months
6	Glottic edema, allergic rhinitis, respiratory diseases with bronchospasm such as asthma and chronic obstructive lung disease
7	Peripheral vascular disease (for example, Raynaud’s syndrome, intermittent claudication)
8	Patients who needs vasopressor support due to prominent volume retention/overload
9	Moderate-to-severe retinopathy (for example, retinal hemorrhage, visual disturbance, retinal microaneurysm within 6 months)
10	Impaired renal function (serum creatinine ≥ 2.5 mg/dL) or hepatic function (AST or ALT ≥ 3 × ULM)
11	Patients in a clinical status that can significantly influence absorption, distribution, metabolism, and secretion of drugs for clinical trials: History of major gastrointestinal surgery, such as gastrectomy or gastric bypass surgery Inflammatory bowel disease within 12 months Current gastric ulcer, pancreatic function abnormality including pancreatitis, gastrointestinal/rectal bleeding which requires treatment Current urologic stenosis or obstruction which requires treatment
12	Confirmed or suspected drug/alcohol abuse within 6 months
13	Pregnant or lactating women, suspected pregnant women or lactating women
14	Chronic inflammatory diseases which require anti-inflammatory treatment
15	Hypersensitivity to carvedilol
16	Malignant disease including lymphoma and leukemia within 5 years
17	Patients who were prescribed other medication for any other clinical trials within the pre-analytical 28 days
18	Patients who are expected to have prolonged hospital stay due to other medical problems other than chronic heart failure (for example, femoral neck fracture)
19	Patients who are considered inappropriate by researchers to participate in the clinical trial

*ALT* alanine transaminase, *AST* aspartate transaminase, *NT-proBNP* N-terminal pro B-type natriuretic peptide, *ULM* upper limit of meta-stability

### Endpoints

The primary endpoint is the change in N-terminal pro B-natriuretic peptide (NT-proBNP) level from baseline to 6 months after randomization. The secondary endpoints include the proportion of patients with NT-proBNP increment > 10% from baseline, composite of all-cause mortality and readmission, mortality rate, readmission rate, change in systolic and diastolic blood pressure at sitting position, control rate and response rate of blood pressure among patients with elevated blood pressure at baseline, quality of life assessed by the Minnesota Living with Heart Failure Questionnaire and Visual Analog Scale, and drug compliance. Table 2 demonstrates the detailed endpoints.

**Table 2 Tab2:** Primary and secondary endpoints

	Endpoint details
Primary endpoint	Change in of NT-proBNP level from baseline to 6 months after randomization
Secondary endpoints	The frequency of NT-proBNP increment > 10% from baseline
	Composite of all-cause mortality and readmission
	All-cause mortality rate and readmission rate
	Change in systolic/diastolic blood pressure at sitting position, control/response rate of blood pressure
	Quality of life assessment by the MLHFQ, Visual Analog Scale
	Drug compliance

*MLHFQ* Minnesota Living with Heart Failure Questionnaire, *NT-proBNP* N-terminal pro B-type natriuretic peptide

### Randomization

Subjects who meet the inclusion and exclusion criteria will be randomly assigned to the carvedilol-SR or carvedilol-IR groups, respectively. The randomization table will be generated by an independent statistician using the SAS system’s randomization program. Restricted block randomization is applied in order to ensure that the subjects are assigned to each group in a balanced manner. At this time, the size of the block will be set by a multiple of 2 (for example, 2, 4, 68, etc.) and it will be implemented using the uniform random-number generator in SAS version 9.2. Web-based randomization will be used and all investigators will be masked to this process until the allocation has been determined.

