## Study limitations

There are several limitations. First, the primary endpoint of our study is the change in NT-proBNP level from baseline to the study end. Although NT-proBNP is a well-validated marker for risk stratification and used as a surrogate marker for clinical outcomes, clinical endpoints, such as mortality and rehospitalization for worsening HF, would be more definitive. Second, there exists a possibility that patients with more advanced HF may be under-represented in this study because they often have fluid volume retention. However, similar findings have been observed in other clinical trials which investigated the effect of beta-blocker management in HF patients [6, 7, 10, 21]. Finally, this is an open-label study.

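### The open-label trial names 2 as a possible block size; allocations become predictable if lists run per centre and sizes are known

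*Protocol article*

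**What the plan says.** The Randomization section of the protocol article gives these elements:

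- **List:** "The randomization table will be generated by an independent statistician using the SAS system’s randomization program".
- **Restriction:** "Restricted block randomization is applied in order to ensure that the subjects are assigned to each group in a balanced manner".
- **Block size:** "the size of the block will be set by a multiple of 2 (for example, 2, 4, 68, etc", and so on. No single size is declared, and nothing is said about whether sizes vary or who may know them.
- **Release:** "Web-based randomization will be used and all investigators will be masked to this process until the allocation has been determined".

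The Overview describes the trial as open-label: "This trial is a prospective, randomized, open-label, phase-IV, multicenter trial to evaluate the efficacy of carvedilol-SR". Study limitations repeats the point: "Finally, this is an open-label study". The abstract gives the ratio and the numbers: patients are "randomly assigned in a 1:1 ratio to the carvedilol-SR group (160 patients) and the carvedilol-IR group (160 patients"). The Carvedilol treatment protocol section has one arm dosed twice a day and the other once a day, so a site cannot mistake which arm a past patient received. The article does not say whether there is one list for the trial or one per centre.

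**The concern.** In a 1:1 block of 2, the first assignment settles the second. In an open-label trial the first assignment is known at the site as soon as treatment starts. The stated safeguard is that "all investigators will be masked to this process until the allocation has been determined". This keeps the next entry from being read off the list, but not from being deduced from entries already revealed.

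Entry leaves room to act on such a deduction. Clinical stability is a judgement, one exclusion criterion rests on the researcher's opinion of suitability, and screening may start up to two weeks before baseline. An investigator who knows the next arm could enrol, defer or pass over a patient accordingly. Baseline prognosis, and with it the change in NT-proBNP, could then differ between arms for reasons unrelated to treatment. In a non-inferiority comparison, a bias that happened to favour carvedilol-SR would help to produce the claim.

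**Working it through.** **Inputs from the protocol article.** Ratio 1:1 with 160 per arm (abstract); 13 centres (Study population); block size an unspecified multiple of 2 (Randomization); SD of change 311.3 pg/ml, margin 110 pg/ml, one-sided alpha 2.5%, power 85%, dropout 10% (Sample size calculation).

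**1. The plan's own figure.** The plan states no figure for predictability. Its sample size reproduces: 2 × (1.960 + 1.036)² × 311.3² / 110² = 143.8, so 144 per arm, and 144 / 0.90 = 160. The present point does not affect it.

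**2. Known, fixed block size, whole sequence visible.** Let a block hold m patients per arm, 2m in all. An allocation is certain once only one arm has places left. The expected length of that final run is 2m/(m + 1), so the certain share is [2m/(m + 1)] / 2m = 1/(m + 1). The correct-guess share comes from listing all balanced orders and always naming the arm with more places left, with a coin toss at ties. For size 2 it is (0.5 + 1)/2 = 75%.

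| Block size | m | Certain in advance | Guessed correctly |
|---|---|---|---|
| 2 | 1 | 1/2 = 50.0% | 75.0% |
| 4 | 2 | 1/3 = 33.3% | 70.8% |
| 6 | 3 | 1/4 = 25.0% | 68.3% |
| 8 | 4 | 1/5 = 20.0% | 66.6% |

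**3. Per-centre list against one central list.** This is a simulation with 4,000 runs. It assumes 8 centres of 25 patients and 5 of 24 (200 + 120 = 320), block sizes drawn with equal probability, and an investigator who sees only the centre's own patients and names the arm with fewer so far.

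| Block sizes | Per-centre list: guessed correctly | Per-centre list: certain from maximum imbalance alone | Central list: guessed correctly |
|---|---|---|---|
| 2 only | 74.4% | 48.8% | 50.5% |
| 2, 4 | 71.5% | 5.4% | 50.6% |
| 2, 4, 6, 8 | 67.9% | 0.14% | 50.5% |
| 4, 6, 8 | 67.1% | 0.14% | 50.6% |

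The first row falls a little below 75% and 50% because a centre with 25 patients stops in mid-block. The third column is a lower bound. For a fixed block of 4 it gives 8.1%, where someone who knows the size has 33.3%.

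**4. What predictability could do to the estimate (illustration).** Assume known blocks of 2 on per-centre lists. Suppose that, whenever the next arm is certain, patient choice shifts the expected change by η in favour of SR if SR is next and by η against IR if IR is next. Half of each arm is then affected, so the between-arm bias is 0.5η + 0.5η = η. For an assumed η of 0.05 to 0.2 SD:

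- 0.05 × 311.3 = 15.6 pg/ml, or 15.6/110 = 14% of the margin;
- 0.2 × 311.3 = 62.3 pg/ml, or 62.3/110 = 57% of the margin.

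Both η and its direction are assumptions. Nothing in the article supplies them.

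**The case against.** The strongest reply is that predicting an allocation takes three things: knowing that the block has size 2, knowing where it starts, and seeing both of its allocations. The article establishes none of them. Size 2 is one example in an open list. Any balanced 1:1 block must be a multiple of 2, so the sentence tells a site little, and naming several sizes is compatible with varying them. An independent statistician makes the list, release is web-based, and no per-centre list is mentioned. All of this stands.

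Three stronger readings are therefore tempting but unsupported:

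- *Concealment fails.* This needs fixed or known blocks and a view of consecutive allocations. With one central list, guessing is close to a coin toss even if every block is 2.
- *The sizes have been disclosed to sites.* The article gives examples. What the full protocol held by sites says is not shown.
- *A block of 68 is intended.* Following 2 and 4, the figure is almost certainly 6, 8 with lost punctuation, and no argument should be built on it.

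It is also fair that an article may leave list structure and custody of the sizes to another document, so their absence alone is no finding. What remains is the positive statement that 2 is an acceptable size in an open-label trial.

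Dropping size 2 by itself also gains little if sizes are mixed and concealed: 67.9% against 67.1% correct guesses on per-centre lists. Finally, the Statistical analysis section plans ANCOVA of the NT-proBNP change. It names no covariates there. Adjustment for baseline NT-proBNP would reduce bias from that variable, but not from prognosis that was not measured.

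**Conclusion.** The point holds as a conditional weakness in a stated design rule. The text permits a single block size of 2 in an open-label trial with visibly different arms, and the masking it describes does not address inference from past allocations. Under per-centre lists with a fixed, known size of 2, half of all allocations would be certain in advance and three quarters guessable. Under one central list over 13 centres the risk is small. The article does not say which applies, so a failure of concealment is possible and not shown, and no bias in a particular direction should be inferred. The exact shares rest only on 1:1 permuted blocks; the simulated shares rest also on the assumed centre sizes and guessing rule. Blocks as small as 2 are not needed for balance with 160 per arm, so a cheap change is worth making.

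**What to change.** For allocations not yet released:

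1. Exclude blocks of 2 and draw sizes at random from a set such as 4, 6 and 8.
2. Keep the sizes in a restricted randomization document that is not shared with sites, and remove example sizes from text that sites hold.
3. Correct 68 (probably 6, 8).

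Random variation and non-disclosure do most of the work. If lists run per centre, correct guesses would still be about 67%, but near-certain prediction largely disappears.

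If blocks of 2 have already been used, compare baseline NT-proBNP between arms separately for the first and second positions in the block. A difference confined to the second position would point to selection.

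The cost is regenerating the unreleased part of the list. The possible final imbalance is at most half the largest block, 8/2 = 4 per list, against 2/2 = 1 with blocks of 2. With a central list that is 4 among 320 patients. With 13 lists the ceiling is 13 × 4 = 52, but only if every centre stopped at its worst point in the same direction.

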### Prohibited drugs during the clinical trial

To avoid drug-drug interactions that may exert confounding effects, drugs with pharmacodynamic and pharmacokinetic interference will be prohibited during the clinical trial (Table 4).

**Table 4 Tab4:** Contraindicated drugs during clinical trial

	Contraindication details
1	Other beta-blockers except the study medication
2	Steroid medication (ACTH or corticosteroid). Locally applied drugs are allowed.
3	Non-steroidal anti-inflammatory drugs. They are allowed only for shor term use (≤7 days) according to the examiner’s decision, while their usage is absolutely prohibited 3 days before the scheduled visits. Low-dose aspirin (30 to 300 mg daily) for cardiovascular diseases is allowed.
4	Estrogen medications. If necessary, low-dose hormonal therapy can be continued for therapeutic purpose at the same dose during the study period
5	Sympathomimetic drugs such as catecholamines
6	Anti-psychotics: MAO inhibitors, anti-depressants (tri- and tetra-cyclic classes, selective serotonin reuptake inhibitors including lithium) Sedatives and anti-anxiolytics (benzodiazepines and their antagonists, barbiturates, hypnotics such as zolpidem) can be intermittently used according to the physician's decision, while their usage is absolutely prohibited 7 days before the scheduled visits
7	Immunosuppressants
8	Thyroid hormones. If necessary, thyroid hormonal therapy can be prescribed for therapeutic purpose at the same dose during the study period

*ACTH* adrenocorticotropic hormone, *MAO* monoamine oxidase

### Clinical follow-up

All patients will be clinically followed up at 2, 4, and 6 months after randomization at each participating center. Each clinic visit comprises history taking, physical examination, laboratory tests, and a 12-lead electrocardiograph (ECG). Drug compliance, adverse effects, and additional concomitant drugs will also be checked. Any unscheduled visit will be recorded. The detailed process is described in Table 5.

**Table 5 Tab5:** Trial process chart

Visit	Visit 1	Visit 2	Visit 3	Visit 4	Visit 5
Status Period	Screening − 2 to 0 week	Baseline 0 months	2 months (± 4 days)	4 months (± 14 days)	6 months (± 14 days)
Inclusion/exclusion criteria	•				
Informed consent	•				
Demographic data	•				
Past medical history^a^	•				
Randomization		•			
Physical examination	•	•	•	•	•
Vital signs	•	•	•	•	•
Height and weight^b^	•	•	•	•	•
Blood analysis^c^	•	•			•
Urinalysis^d^	•	•			•
Pregnancy test^e^	•	•			•
Chest x-ray^f^	•				
12-lead electrocardiograph^g^	•				•
Echocardiography^h^	•	•			•
Concomitant medication	•	•	•	•	•
Adverse events		•	•	•	•
Patient’s compliance			•	•	•
Questionnaire for quality of life		•			•

^a^The history of diseases, medications, and operations will be recorded

^b^Check weight only after visit 2

^c^CBC: WBC with differential count, hemoglobin, hematocrit, platelets; chemistry: albumin, total protein, triglycerides, high-density lipoprotein-cholesterol, low-density lipoprotein-cholesterol, blood urea nitrogen, serum creatinine, uric acid, total bilirubin, AST, ALT, ALP, NT-proBNP, hs-CRP; electrolytes: Na, K, Ca, Cl, P

^d^Specific gravity, pH, albumin (protein), glucose, blood (occult blood), urobilinogen, ketones

^e^Women of child-bearing age

^f,g^Examination at visit 6 can be optionally performed according to the examiner’s decision

^h^Follow-up echocardiograph, if available

